# A Phase II, Randomized, Double-blind, Controlled Safety and Immunogenicity Trial of Typhoid Conjugate Vaccine in Children Under 2 Years of Age in Ouagadougou, Burkina Faso: A Methods Paper

**DOI:** 10.1093/cid/ciy1104

**Published:** 2019-03-07

**Keywords:** child, typhoid-paratyphoid vaccines, Burkina Faso, immunogenicity, conjugate

## Abstract

The recent Typhoid Fever Surveillance in Africa Program demonstrated an overall adjusted incidence of typhoid fever 2–3 times higher than previous estimates in Africa. Recently, a single-dose typhoid conjugate vaccine that allows infants as young as 6 months old to be vaccinated was prequalified by the World Health Organization (WHO). This Vi-based conjugate vaccine demonstrated robust immunogenicity after 1 dose in infants and children 6 through 23 months of age in India with no safety signal, and is currently being tested for the first time on the African continent in Malawi. The WHO Strategic Advisory Group of Experts recommends studies to evaluate co-administering Vi-typhoid conjugate vaccine (Vi-TCV) with routine childhood vaccines in typhoid-endemic countries. The Burkina Faso immunization schedule includes yellow fever vaccine (YFV) at 9 months and meningococcal A conjugate vaccine (MCV-A) at 15 months, in addition to measles-rubella vaccine at both 9 and 15 months. Co-administration testing of Vi-TCV with these routine vaccinations will provide the data needed to support large-scale uptake of Vi-TCV in sub-Saharan Africa. A randomized, controlled, Phase II trial of Vi-TCV co-administration with the vaccinations routinely given at 9 and 15 months of age is planned in Burkina Faso. The overall aim is to assess the safety and immunogenicity of Vi-TCV when co-administered with YFV at 9 months of age and with MCV-A at 15 months of age. A total of 250 participants (100 infants aged 9–11 months and 150 children aged 15–23 months) will be enrolled.

***Clinical Trials Registration.*** NCT03614533.

Estimating the typhoid fever incidence is challenging in low- and middle-income countries, due to the non-specific clinical disease presentation and limited access to blood cultures, the most reliable laboratory diagnostic. The recent Typhoid Fever Surveillance in Africa Program measured the incidence of invasive *Salmonella* bloodstream infections in 10 African countries over a 27-month period [1] and demonstrated an overall adjusted incidence of typhoid fever 2–3 times higher than previous estimates [2]. Importantly, 47% of *Salmonella enterica* serovar Typhi isolates were multidrug resistant. Similar studies have documented a significant burden of typhoid fever in sub-Saharan Africa [3–6]. In Burkina Faso, the adjusted incidence of *S*. Typhi ranged from 104 to 383 per 100 000 person-years of observation (PYO) for all ages across 2 study sites. The highest adjusted incidence occurred in children 5–14 years of age at Nioko II (315 per 100 000 PYO) and in children 2–4 years of age at Polesgo (1890 per 100 000 PYO) [1].

In addition to clean water and adequate sanitation, the World Health Organization (WHO) recommends vaccination against typhoid fever as an effective preventive measure. Before 2017, only 2 typhoid vaccines were available [7]: (1) the oral, live-attenuated Ty21a vaccine, licensed for children ≥6 years of age, and (2) an injectable Vi capsular polysaccharide vaccine, licensed for children ≥2 years of age. Recently, Bharat Biotech International developed a conjugate vaccine (Typbar-TCV) with Vi polysaccharide conjugated to a nontoxic tetanus toxoid (TT) protein carrier. This Vi-typhoid conjugate vaccine (Vi-TCV) stimulates both a strong, T-cell–dependent response and a more robust, anti-Vi response as compared to an unconjugated Vi polysaccharide vaccine. Vi-TCV safety and immunogenicity have been studied in adults and children as young as 6 months of age in India [8], where a single dose elicited 4-fold seroconversion rates of 98% and 99% in participants 6–23 months and 2–15 years, respectively [8]. This vaccine holds significant promise, because of its single-dose schedule and utility in infants as young as 6 months of age.

While Vi-TCVs have been extensively studied in Asia, an ongoing clinical trial of Typbar-TCV in Malawian infants and children is the first-ever trial of any Vi-TCV in Africa [9]. This study will provide valuable data to sub-Saharan African decision-makers. However, because Expanded Program on Immunization (EPI) schedules differ throughout the continent, the WHO Strategic Advisory Group of Experts recommends studies to evaluate co-administering Vi-TCV with routine childhood vaccines in typhoid-endemic countries.

Available data from Asia on Typbar-TCV co-administration with measles-containing vaccines shows no altered immune response to either product; this result is being confirmed in Malawi in an immunogenicity sub-study of measles-rubella vaccine (MR) co-administration with Typbar-TCV [9]. Co-administration studies with yellow fever vaccine (YFV) and meningococcal A conjugate vaccine (MCV-A) are needed. Burkina Faso is the ideal study site, given its elevated burden of typhoid fever, elevated infant mortality, high malaria prevalence, ongoing typhoid surveillance, existing research infrastructure, and history of early introduction of WHO pre-qualified vaccines. The Burkina Faso immunization schedule includes YFV at 9 months and MCV-A at 15 months, in addition to MR at both 9 and 15 months.

## TRIAL OVERVIEW

A randomized, controlled, Phase II trial will test Vi-TCV co-administration with vaccinations routinely given at 9 and 15 months of age in Burkina Faso. Our aim is to assess the safety and immunogenicity of Vi-TCV when co-administered with vaccinations routinely given to children at both 9 and 15 months of age in Burkina Faso. The Vi-TCV vaccine or an inactivated poliovirus vaccine (IPV) will be administered. Children 9–11 months of age will be randomized 1:1 to Vi-TCV or IPV; children 15–23 months of age will be randomized 1:1:1 to Vi-TCV + MCV-A, Vi-TCV + IPV with delayed MCV-A, or MCV-A + IPV. We will use block randomization with varying block sizes from 6–12. Our study objectives and endpoints are listed in Table 1.

**Table 1. T1:** Primary, Secondary, and Exploratory Objectives and Endpoints

	Objectives	Endpoints
**Primary**	To assess the safety of Vi-TCV when co-administered with Expanded Program on Immunization vaccines among children 9–11 months of age and 15–23 months of age in Burkina Faso.	1. Proportion of participants who develop adverse events in the first 30 minutes after vaccination and for 7 days after vaccination. 2. Proportion of participants who experience SAEs within 6 months of vaccination, in all participants. 3. Proportion of participants who experience other, non-serious adverse events up to 28 days following vaccination.
**Secondary**	1. To assess the immunogenicity of YFV when given with and without Vi-TCV in children 9–11 months of age. 2. To assess the immunogenicity of MCV-A when given with and without Vi-TCV in children 15–23 months of age. 3. To assess the immunogenicity of Vi-TCV when given with YFV in children 9–11 months of age. 4. To assess the immunogenicity of Vi-TCV when given with and without MCV-A in children 15–23 months of age.	1. Immunogenicity of YFV: yellow fever plaque reduction neutralization test at Days 0 and 28 in infants 9–11 months of age. 2. Immunogenicity of MCV-A: serum bactericidal antibody assay against *Neisseria meningitidis* serogroup A at Days 0 and 28 in children 15–23 months of age. 3. Immunogenicity of Vi-TCV when given with YFV: anti-Vi IgG antibody titer, as measured by ELISA at Days 0 and 28 in infants 9–11 months of age. 4. Immunogenicity of Vi-TCV when given with and without MCV-A: anti-Vi IgG antibody titer, as measured by ELISA at Days 0 and 28 in infants 9–11 months of age.
**Exploratory**	1. To assess the TT IgG antibody levels in children of all ages who receive any vaccine regimen. 2. To assess whether the presence of *P. falciparum* parasitemia is associated with a decreased immunogenic response to vaccination with YFV, Vi-TCV, TT, and MCV-A.	1. Anti-TT IgG antibody level in all children who receive any vaccine regimen. 2. Immunogenicity of YFV, Vi-TCV, TT, and MCV-A in vaccinated children with and without *Plasmodium falciparum* parasitemia present at vaccination.

Abbreviations: ELISA, enzyme-linked immunosorbent assay; IgG, immunoglobulin G; MCV-A, meningococcal A conjugate vaccine; SAE, serious adverse event; TT, tetanus toxoid; Vi-TCV, Vi-typhoid conjugate vaccine; YFV, yellow fever vaccine.

Following the routine vaccination schedule, the vaccines will be administered to all participants per Burkina Faso Ministry of Health guidelines, except for 1 group of 50 children aged 15–23 months of age, who will delay MCV-A by 1 month. We anticipate recruiting 250 participants (100 infants aged 9–11 months and 150 children aged 15–23 months) at a study site in Ouagadougou, Burkina Faso. The study duration (recruitment and follow-up) will be approximately 9 months. A trial schedule of events is found in Table 4.

This study is sponsored by the Center for Vaccine Development and Global Health at the University of Maryland School of Medicine in Baltimore, Maryland.

## METHODS

This study will be divided into 2 cohorts, by age, with separate study designs. Cohort 1 will include children 9–11 months of age. Cohort 2 will include children 15–23 months of age. The purpose for our detailed evaluation of safety and immunogenicity is to assess vaccine reactogenicity and the immune response to Vi-TCV and co-administered vaccines. Serum will be collected from all participants on Day 0 (before vaccination) and on post-vaccination Day 28 to quantify anti-Vi and anti-TT antibodies. All children will have an additional 0.5 mL of blood collected on Day 0, before the study vaccination, to test for the presence of malaria parasitemia at baseline. Some studies demonstrate impaired immunogenicity of routine vaccinations in children with *Plasmodium**falciparum* malaria at sites similar to Ouagadougou [10–12], and we will evaluate this potential effect by measuring for *P. falciparum* parasitemia on Day 0.

Children 9–11 months of age will be eligible for Cohort 1, a double-blind, individually randomized, controlled trial. Up to 100 children will be randomized in a 1:1 ratio to receive Vi-TCV (Group 1) or IPV (Group 2). Participants and parents will not know the study vaccine received. Vi-TCV or IPV will be administered with MR and YFV, as per Burkina Faso’s EPI schedule. These 9–11-month-old children will have immunogenicity to Vi-TCV, YFV, and TT assessed on Days 0 and 28.

Children 15–23 months of age will be eligible for Cohort 2, a randomized safety and immunogenicity study of (1) Vi-TCV when co-administered with routine EPI vaccines (MCV-A and MR) or given alone and (2) MCV-A when co-administered or given alone. Participants in this cohort (up to 150) will be randomized 1:1:1: Group 3 participants will receive Vi-TCV and IPV at Day 0, with a subsequent dose of MCV-A at Day 28; Group 4 will receive MCV-A and Vi-TCV at Day 0; and Group 5 will receive MCV-A and IPV at Day 0. All children will receive MR at Day 0. Cohort 2 will be unblinded on Day 28 for safety and follow-up and to ensure MCV-A receipt in Group 3. These 15–23-month-old children will have serum bactericidal antibodies to *Neisseria meningitidis* serogroup A, anti-Vi antibody, and TT antibody assessed on Days 0 and 28.

We will measure anti-Vi immunoglobulin G (IgG) antibody responses using the VaccZyme Salmonella typhi Vi IgG enzyme-linked immunosorbent assay commercial kit (The Binding Site Group Ltd, Birmingham, UK). Antibody titers will be expressed as enzyme-linked immunosorbent assay units per milliliter (U/mL). Both anti-Vi IgG antibody geometric mean titers and seroconversion, defined as a 4-fold or greater rise in anti-Vi antibody titers from baseline, will be calculated per group. The difference in geometric mean titers between the 2 groups will be compared using a 2-sample Student *t* test on log-transformed titers or a Mann-Whitney U test, as appropriate. The difference in the percentages of participants who seroconverted between the 2 groups will be compared using the Pearson’s chi-square test or Fisher’s exact test, as appropriate.

Participants in both cohorts will have home or clinic visits on Days 3 and 7 following vaccination, for local and systemic adverse event (AE) capture. Non-serious AEs will be assessed up to Day 28. Serious adverse events (SAEs) will be captured throughout the study follow-up.

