### Blinding

Vi-TCV and IPV have similar pharmaceutical presentations. Unblinded study personnel will be responsible for vaccine preparation and administration. These unblinded personnel will not be involved in study-related assessments or have contact with subjects for the purpose of data collection following the study vaccination. Study participants, their family members, and study staff will not know the assigned vaccine group. The 15–23-month-old cohort will be unblinded on Day 28, so that Group 3 can receive MCV-A at this visit.

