### Follow-up

Follow-up visits may be either routine or unscheduled. Routine visits will occur on Days 3, 7, 28, and 180. On Days 3 and 7 following vaccination, participants will be asked to return to the study clinic to assess reactogenicity. During these visits, solicited and unsolicited AEs will be recorded. Alternatively, these visits may be conducted in the home. On Day 28 following vaccination, participants will be asked to return to the study clinic for a follow-up visit. During this visit, the treatment groups in the 15–23-month-old cohort will be unblinded, participants will have approximately 3–5 mL of blood drawn to measure the Vi antibody responses for typhoid (all age groups), measure the TT serum IgG antibody levels (all age groups), and conduct the yellow fever plaque reduction neutralization testing (9–11-month-old group only) or measure the meningococcal A serum bactericidal antibody titers (15–23-month-old group only), which will be used for the primary and secondary objectives, as listed. Participants will have their final visit on Day 180, when interim SAEs will be recorded.

During unscheduled visits, participants will undergo standard procedures for the evaluation and treatment of illness, as defined by the Ministry of Health. Illnesses and other medical issues will be documented as AEs in participant records, and their seriousness, severity, relationship to the study product, and expectedness will be recorded.

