## ADVERSE EVENTS

### Immediate Reactions

All participants will be observed for immediate reactions for 30 minutes after vaccination. Immediate reactions will be assessed by a study physician or appropriately trained medical staff member, and recorded on the appropriate case report form (CRF).

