## DISCUSSION

This randomized, controlled clinical trial among infants and young children in Ouagadougou, Burkina Faso, will be the first in West Africa to test the pre-qualified Typbar-TCV. The study will provide the first information on co-administration of this vaccine with YFV and MCV-A, as recommended by the WHO. The rationale for the 3 arms in the older children is that both MCV-A and TCV contain tetanus toxoid as the carrier protein: thus, our study design allows us to carefully assess reactogenicity when those vaccines are given alone or together, and evaluate any effect on the antibody responses that might occur with a shared carrier protein. Such a phenomenon was noted with *Haemophilus Influenzae* Type b vaccines [18] and is thought to occur due to interference by a common protein carrier with common immunogenic epitopes [19]. We did not include an assessment of measles and rubella antibody responses, since this has been previously tested and we have attempted to minimize blood collection volumes in these young children.

Malaria parasitemia is prevalent among young children in Burkina Faso. We will test for *P. falciparum* parasitemia at Day 0 to evaluate the potential effect on the immunogenicity of Typbar-TCV and of the other vaccines administered.

**Table 4. T4:** Trial Schedule of Events. Abbreviations: AE, adverse event; SAE, serious adverse event.

Study Visit Type	Recruitment	Screening	Eligibility, enrollment, vaccination	Follow up	Follow up	Follow up	Follow up	Early termination
Study Visit Number		V00	V01	V02	V03	V04	V05	
Study Time point			D0	D3	D7±1	D28±3	D180±7	
Study introduction, recruiting	X	X^a^	X^a^					
Obtain informed consent		X	X^a,b^					
Review eligibility criteria		X	X^a,c^					
Review medical history		X	X^a,c^	X^c^	X^c^	X^c^	X^c^	X^c^
Review concomitant meds		X	X^a,c^	X^c^	X^c^	X^c^	X^c^	X^c^
Review vaccination history		X	X^a,c^	X^c^	X^c^	X^c^		X^c^
Axillary temperature^d^		X	X^e^			X		X
Height and weight and Middle Upper Arm Circumference (MUAC)		X	X^e^				X	X
Targeted physical exam		X^˚^	X^a,c,e,˚^			X^c,˚^		X^c,˚^
Vaccination			X			X^f^		
30-min post-vaccination evaluation			X					
Post-vaccination reactogenicity assessment				X	X			X
Venous blood collection for immunogenicity			X^e,g^			Xg		X^g^
Venous blood collection for malaria parasitemia			X^e^					
Assess and record SAES			X^h^	X	X	X	X	X
Assess and record solicited AEs			X^h^	X	X			X^i^

^a^If not performed at previous visit.

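### Unblinding the whole of Cohort 2 at Day 28 also reveals Group 4 versus Group 5, which the delayed MCV-A dose does not require, and opens most of the 6-month SAE window for that contrast

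*Protocol article*

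**What the plan says.** The protocol article describes the unblinding in three places, and they agree on its scope.

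- Methods (Cohort 2): "Cohort 2 will be unblinded on Day 28 for safety and follow-up and to ensure MCV-A receipt in Group 3".
- Blinding: "The 15–23-month-old cohort will be unblinded on Day 28, so that Group 3 can receive MCV-A at this visit". This section gives the MCV-A dose as the only reason.
- Follow-up, on the Day 28 visit: "the treatment groups in the 15–23-month-old cohort will be unblinded".

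In Methods, Group 3 receives Vi-TCV and IPV on Day 0 and MCV-A on Day 28. Group 4 receives MCV-A and Vi-TCV on Day 0, and Group 5 receives MCV-A and IPV on Day 0. All three groups receive MR on Day 0.

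The second primary endpoint in Table 1 is: "Proportion of participants who experience SAEs within 6 months of vaccination, in all participants". Follow-up places the last visit at Day 180, when SAEs since the previous visit are recorded.

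On observation after vaccination, the Immediate Reactions section says: "All participants will be observed for immediate reactions for 30 minutes after vaccination". Table 4 marks vaccination at V01 and, for Group 3 only, at V04 (Day 28). Its row "30-min post-vaccination evaluation" is marked at V01 alone.

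**The concern.** The unblinding is wider than the need given for it. What staff must know at Day 28 is whether a child is still due MCV-A. That separates Group 3 from Groups 4 and 5 taken together, and says nothing about who in Groups 4 and 5 had Vi-TCV and who had IPV. Yet that is the one comparison in the older cohort where Vi-TCV is exchanged for a control vaccine with everything else equal.

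The cost falls on a primary endpoint. After Day 28 the only scheduled contact is Day 180. Apart from unscheduled visits, SAE capture over that period depends on what parents recall and report, and on when they seek care. By then parents and assessors may know the assignment. Some of the recording also involves judgement: the Seriousness of Event section admits other important medical events, and Follow-up has staff rate seriousness, severity and relatedness of illnesses seen at unscheduled visits. An analysis plan written later cannot restore masking once it is lost.

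Two smaller matters belong to the same visit. Group 3 is vaccinated again inside the SAE window, and the article does not separate its events before and after that dose. The text and Table 4 also differ on whether the 30-minute observation applies at that vaccination.

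**Working it through.** **1. Who must be identified at Day 28 (regimens from Methods)**

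| Group | Day 0 (all with MR) | MCV-A due at Day 28? |
|---|---|---|
| 3 | Vi-TCV + IPV | yes |
| 4 | MCV-A + Vi-TCV | no |
| 5 | MCV-A + IPV | no |

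A two-state code (due, not due) is enough. It necessarily reveals Group 3 but leaves Groups 4 and 5 masked from each other.

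**2. Share of the SAE window that is open-label**

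Inputs: unblinding at Day 28 (±3) and last visit at Day 180 (±7), from Table 4.

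- Nominal: (180 − 28)/180 = 152/180 = 84.4%.
- Late unblinding, early last visit: (173 − 31)/173 = 82.1%.
- Early unblinding, late last visit: (187 − 25)/187 = 86.6%.

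**3. Child-days, taking 50 per group and no dropout**

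- Groups 4 and 5 as planned: 100 × 152 = 15,200 of 100 × 180 = 18,000, or 84.4%. With the two-state code: 0.
- Cohort 2 as planned: 150 × 152 = 22,800 of 150 × 180 = 27,000, or 84.4%. With the code: 50 × 152 = 7,600 of 27,000, or 28.1%, all in Group 3.

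**4. From days to events**

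The article gives no SAE rate, so this is an assumption: a 6-month risk r between 1% and 10% with constant hazard h = −ln(1 − r)/180. The share of first SAEs after Day 28 is [exp(−28h) − exp(−180h)]/r.

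- r = 1%: 0.844, with 50 × 0.01 = 0.5 children with an SAE expected per group.
- r = 10%: 0.837, with 50 × 0.10 = 5 children per group.

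The share is therefore about 84% throughout, but of few events. The same share of Group 3's SAEs would fall after its MCV-A dose.

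**5. The plan's own figures**

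Table 3 gives no power for the SAE endpoint. For Group 4 v 5 it gives 80% for 7-day reactogenicity, 10% v 33% with 45 per group. The unpooled z-test gives SE = √(0.10 × 0.90/45 + 0.33 × 0.67/45) = 0.0831, then 0.23/0.0831 − 1.96 = 0.81, so power is 0.79. The stated figure is reproduced to within about one point. Those data are complete by Day 7, before unblinding, so this point does not change it.

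**6. Thirty-minute observation**

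Immediate Reactions covers all participants after vaccination. Table 4 shows a vaccination at V04 for Group 3 but no 30-minute evaluation in that column. The two do not match.

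**The case against.** The case for leaving the plan alone has real substance.

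- **The choice is deliberate and disclosed.** Three sections agree. Methods says the cohorts have separate designs and applies the term double-blind only to Cohort 1, although the title applies it to the whole trial. This stands: there is no contradiction about the unblinding itself.
- **A second reason is given.** Methods also cites safety and follow-up, and an article need not expand on it. A reader might infer that about 100 children lose masking with no operational need. The documents do not support that; they show only that the reason is unexplained and that nothing named requires Group 4 to be told from Group 5.
- **The endpoint is mostly hard.** Death, threat to life, hospitalization and disability leave little room for judgement, and endpoint 2 counts SAEs whether or not they are related. This stands and limits the size of the concern.
- **The other safety endpoints are protected.** Reactogenicity closes at Day 7 and non-serious AEs at Day 28. This stands. The order of steps within the Day 28 visit is a detail that an article may leave to the full protocol, so its absence is not counted here.
- **Group 3 v 4.** A reader might infer that a 6-month comparison of SAEs between Groups 3 and 4 is confounded by the second vaccination. Table 3 plans no such comparison. For that pair it has only 7-day reactogenicity and anti-Vi seroconversion, both resting on data collected no later than Day 28. SAEs to Day 180 are a fair description of the regimen Group 3 was assigned, which includes the delayed dose. Only a matter of presentation remains.
- **Laboratory.** Nothing says laboratory staff learn the assignments, so no claim about assay bias can be made.

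What none of this answers is that the reason given in the Blinding section does not require separating Groups 4 and 5, and that keeping them masked is nearly free.

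**Conclusion.** The concern holds in a limited form. The plan unmasks Group 4 versus Group 5 at Day 28 without a stated reason that requires it. This leaves 84% (82% to 87% across the visit windows) of the 6-month SAE window open-label for the older cohort's only contrast of Vi-TCV against control.

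This affects one of three primary endpoints, and only after Day 28. It would be too strong to call the SAE endpoint open-label throughout, or to read 84% as a measure of bias: it is a share of follow-up time. It becomes a share of events only under a constant SAE rate, with assumed risks that imply 0.5 to 5 affected children per group. Any bias would act through parental reporting, care seeking and the judged categories, and is likely to be modest. No sample size or power figure changes.

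The change is worth making because it is simple and the loss cannot be repaired later. Separating Group 3's SAEs by time is a presentation point. The mismatch between Immediate Reactions and Table 4 is a genuine inconsistency, separate from the blinding question.

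**What to change.** 1. **Narrow the unblinding.** In Methods, Blinding and Follow-up, replace the whole-cohort unblinding with wording such as: *At Day 28, after AE collection and the blood draw, unblinded vaccine staff disclose only whether MCV-A is due. The Vi-TCV or IPV assignment in Groups 4 and 5 remains masked to families and assessors until Day 180.* If the sponsor has a safety or follow-up reason that needs Groups 4 and 5 told apart, the protocol should state it.
2. **Present Group 3's SAEs in two periods**, before and after its Day 28 MCV-A dose, alongside the total to Day 180. Keep Group 4 v 5 for the full 6 months.
3. **Reconcile** the Immediate Reactions section with the V04 column of Table 4 for Group 3's Day 28 vaccination. Which of the two is intended is for the sponsor to settle.

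Cost: amended wording, a two-state code list held by the unblinded staff the trial already has, and one extra split in a safety table. The downside is that families in Groups 4 and 5 learn their child's assignment at Day 180 instead of Day 28. No extra visits, samples or participants are needed.

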### Analysis

Study hypotheses and power analyses are found in Table 3. The intention-to-treat population includes all randomized individuals, in the vaccine groups to which they were assigned, and all follow-up time, beginning with the time of randomization. The primary analysis will be based on this population. The per-protocol population includes all vaccinated individuals, in the vaccine groups based on the vaccines they received. Additional details of study analyses will be included in a statistical analysis plan, which will be written by the study biostatistician before the study’s data analysis begins.

**Table 3. T3:** Study Hypotheses and Power Analyses.

	Hypothesis	Power Analysis
**Cohort 1:** Children 9–11 months of age (n = 100), enrolled in a double-blind, individually randomized, controlled trial. With an expected 10% dropout rate, we anticipate 90 children (90% of 100 enrolled) will complete follow-up assessments: 45 in Group 1 and 45 in Group 2.	Reactogenicity following Vi-TCV given together with YFV and MR (Group 1) is not significantly different from reactogenicity following IPV given together with YFV and MR (Group 2).	The expected incidence of any grade 2 or greater solicited, systemic adverse events over 7 days following vaccination is 10% in Group 2 [14]. Sample sizes of 45 in Group 1 and 45 in Group 2 achieve 80% power to detect a minimum difference of 0.23 (= 33% - 10%), using a 2-sided z-test with unpooled variance and a significance level of 5% (PASS 15).
	The percentage of participants with seroconversion (≥2-fold rise) in yellow fever neutralizing antibodies following a single dose of Vi-TCV given together with YFV and MR (Group 1) is not significantly different from the percentage of participants with seroconversion (≥2-fold rise) in yellow fever neutralizing antibodies following a single dose of IPV given together with YF and MR (Group 2).	In Group 2, the expected seroconversion proportion is 70% [14]. Sample sizes of 45 in Group 1 and 45 in Group 2 achieve 80% power to detect a minimum difference of 0.28 (= 70% - 42%), using a 2-sided z-test with unpooled variance and a significance level of 5% (PASS 15).

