	The percentage of participants with seroconversion (≥4-fold rise) in Anti-Vi IgG antibodies following a single dose of Vi-TCV given together with IPV and MR (Group 3) is not significantly different from the percentage of participants with seroconversion (≥4-fold rise) in Anti-Vi IgG antibodies following a single dose of Vi-TCV given together with MCV-A and MR (Group 4).	In Group 3, the expected seroconversion proportion is 95% [8]. Sample sizes of 45 in Group 3 and 45 in Group 4 achieve 80% power to detect a minimum difference of 0.20 (= 95% - 75%), using a 2-sided z-test with unpooled variance and a significance level of 5% (PASS 15).

Abbreviations: IgG, immunoglobulin G; IPV, inactivated poliovirus vaccine; MCV-A, meningococcal A conjugate vaccine; MR, measles-rubella vaccine; Vi-TCV, Vi-typhoid conjugate vaccine; YFV, yellow fever vaccine.

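### The anti-Vi GMT comparison makes no use of the Day 0 titer and allows a Mann-Whitney test, which does not test the geometric-mean difference it names

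*Protocol article*

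**What the plan says.** The immunogenicity paragraph of Methods (protocol article) first names the quantity and one test: "The difference in geometric mean titers between the 2 groups will be compared using a 2-sample Student". It then completes the choice: "test on log-transformed titers or a Mann-Whitney U test, as appropriate". No covariate, criterion for choosing, comparison day or pair of groups is named.

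On the baseline sample, Methods states: "Serum will be collected from all participants on Day 0 (before vaccination) and on post-vaccination Day 28 to quantify anti-Vi and anti-TT antibodies". The Day 0 anti-Vi titer has one stated use in the Vi analysis, again in the immunogenicity paragraph: "seroconversion, defined as a 4-fold or greater rise in anti-Vi antibody titers from baseline, will be calculated per group".

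Table 1 lists the titer as a secondary endpoint: "Immunogenicity of Vi-TCV when given with and without MCV-A: anti-Vi IgG antibody titer, as measured by ELISA at Days 0 and 28". (That row gives the younger age group. Objective 4 of the same table, and Table 3, place the comparison in children of 15–23 months, and I follow them.) Table 3 powers Vi on seroconversion, Group 3 against Group 4, and gives no SD or power for titers. On what is left for later, the Analysis section says: "Additional details of study analyses will be included in a statistical analysis plan, which will be written by the study biostatistician".

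**The concern.** Two things look wrong.

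First, a randomized comparison of post-vaccination titers is planned with no baseline term, although the baseline titer is measured in every child. Any Day 0 to Day 28 correlation is then left in the error variance.

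Second, one named quantity is paired with two tests that do not share a target. A t test on log titers tests equality of mean log titers, and its estimate back-transforms to a GMT ratio with a confidence interval. Mann-Whitney tests whether values in one group tend to exceed those in the other. It gives no GMT ratio, and its result need not agree with one.

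This matters because the Discussion gives a shared tetanus toxoid carrier as the reason for three arms in the older cohort. Vi seroconversion is expected at 95%, and Table 3 can detect only a fall to 75%. A lower titer could leave seroconversion near its ceiling, so the GMT ratio is a useful second view of interference, and it should be clear what is being estimated.

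**Working it through.** **Inputs from the article.** Cohort 2 has 150 children randomized 1:1:1 with 10% dropout: 150 × 0.9 / 3 = 45 per group. Vi seroconversion is 95% against 75%, tested two-sided at 5% with an unpooled z-test and 80% power (Table 3). Prior typhoid vaccine is an exclusion (Table 2).

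**Inputs not in the article, so assumed.** The SD of log10 titer (0.3 to 0.6) and the Day 0 to Day 28 correlation rho (0 to 0.7).

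**Step 1: the plan's own Vi figure.** Unpooled standard error = √[(0.95 × 0.05 + 0.75 × 0.25) / 45] = √(0.235 / 45) = 0.0723. Power = Φ(0.20 / 0.0723 − 1.96) = Φ(0.81) = 79.0%. The stated 80% reproduces to within rounding. It concerns seroconversion and is unaffected by what follows.

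**Step 2: gain from the Day 0 titer.** Adjustment multiplies the residual variance by 1 − rho². Take an effect that the unadjusted t test detects with 80% power at 45 per group (normal approximation, ignoring the one degree of freedom spent):

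- Power = Φ[(1.96 + 0.84) / √(1 − rho²) − 1.96]
- Equivalent unadjusted size per group = 45 / (1 − rho²)
- Detectable GMT ratio = 10^[(1.96 + 0.84) × SD × √(1 − rho²) × √(2/45)], shown for SD 0.4

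| rho | 1 − rho² | equivalent n per group | power | detectable GMT ratio |
|---|---|---|---|---|
| 0 | 1.00 | 45 | 80.0% | 1.72 |
| 0.1 | 0.99 | 45.5 | 80.4% | 1.72 |
| 0.2 | 0.96 | 46.9 | 81.6% | 1.70 |
| 0.3 | 0.91 | 49.5 | 83.6% | 1.68 |
| 0.5 | 0.75 | 60 | 89.9% | 1.60 |
| 0.7 | 0.51 | 88.2 | 97.5% | 1.47 |

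For rho 0, 0.3 and 0.5, the detectable ratio is 1.50, 1.48 and 1.42 at SD 0.3, and 2.26, 2.18 and 2.03 at SD 0.6.

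Comparing fold rises instead is not an equivalent repair. With equal SDs on the two days, the variance of the change is 2(1 − rho) times the Day 28 variance: 2.0 at rho 0, 1.6 at 0.2 and 1.0 at 0.5. At low correlation it is worse than ignoring Day 0.

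**Step 3: does the open choice of test break the error rate?** Simulation with 45 per group and 20,000 null runs at nominal 5%:

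- Normal log titers: t test 4.9%, Mann-Whitney 4.8%, choice by a Shapiro pre-test 5.0%.
- With 5% non-responders in both groups: 5.0% for all three.
- Reporting whichever p-value is smaller: 5.8% and 7.0% respectively.

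**Step 4: do the two tests see the same thing?** Simulated power, 5,000 runs, 45 per group:

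- Pure shift of 0.236 in log10 titer, SD 0.4: t test 80%, Mann-Whitney 77%.
- 5% against 25% non-responders (log10 mean 0.6, SD 0.2) with identical responders (mean 3, SD 0.4): t test 69%, Mann-Whitney 37%.

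Under a pure shift the choice hardly matters. When the groups differ in the share of non-responders it matters a good deal, because the quantities tested differ.

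**The case against.** The best case on the other side is that this is SAP detail. The article defers further analysis details to an SAP due before data analysis begins, and covariates and the rule behind the choice of test commonly sit there. That would answer a complaint that something is missing. It does not fully answer this one, because the article already fixes an unadjusted pair of tests, and an SAP that followed it would inherit the mismatch.

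Several stronger readings are tempting and are not supported:

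- A reader might infer that the Day 0 titer is thrown away. It is not. It defines seroconversion, which is compared between groups and is the powered Vi outcome.
- A reader might infer bias. Under randomization the unadjusted t test is valid, and it gives a GMT ratio with an interval directly.
- A reader might infer that the test will be picked after seeing the results. The article gives no criterion and no timing, and the SAP could fix the rule. A pre-test choice did not inflate the error rate in Step 3. Only picking the smaller p-value did, and nothing in the article suggests that.
- A reader might take 60 per group as the expected gain. It needs rho 0.5, which the article does not support. With prior typhoid vaccine excluded and 95% expected to show at least a fourfold rise, rho for Vi may well be low.

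It is also fair to say that the sharp divergence in Step 4 rests on a 95% against 75% response contrast, which the seroconversion test already targets. GMTs are to be calculated per group whichever test is used. What remains is the mismatch between the named quantity and Mann-Whitney, and a baseline measurement left unused in this comparison.

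**Conclusion.** The point holds as a modest improvement to a secondary comparison for which no power is stated. The mismatch stands whatever rho is: under one of its two branches, the plan does not test the GMT difference it names.

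The precision loss depends wholly on rho, which the documents do not give. At rho up to 0.3 adjustment adds at most about 4 power points (80% to 83.6%), and at 0.5 about 10 (to 89.9%). If most children have Day 0 Vi titers below the detection limit, the gain will be near zero. The detectable GMT ratios also rest on an assumed log10 SD.

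No stated sample size or power changes, since Table 3 is built on seroconversion and reactogenicity. The article names a titer test for anti-Vi only, so the point does not extend to a fault in the yellow fever, meningococcal A or tetanus toxoid analyses.

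**What to change.** For this secondary comparison, replace the open choice with one named analysis:

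- **Quantity:** the Day 28 anti-Vi GMT ratio, Group 4 / Group 3, with a 95% CI.
- **Model:** linear regression of log titer on group with log Day 0 titer as covariate, back-transformed.
- **Values below the detection limit:** a stated substitution, applied alike to Day 0 and Day 28.
- **Mann-Whitney:** kept only as a named sensitivity analysis, described as a comparison of distributions and not of GMTs.

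The same model may be used for the other antibody titers as an option.

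The cost is a line or two in the SAP, settled before data analysis. It needs no new samples and no change in sample size. The one added burden is the substitution rule, which matters more once Day 0 titers enter as a covariate.
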